*Mental health assessment*. This will be assessed using the Sports Mental Health Assessment Screening Tool-1 (SMART-1). The SMART-1 is a standardised assessment tool that aims to identify individual athletes potentially at risk for or already experiencing mental health symptoms and disorders to facilitate timely referral for those in need of support or treatment [42].

*Football exposure*: *Injury*, *illness*, *and medication use surveillance*. These data will be collected at a cluster level using injury, illness and football load forms as recommended in injury consensus statements [36]. The research team will follow up with each football nurse on a weekly basis to ensure surveillance data is being captured. Should an injury occur that requires investigations or further management, the nurses will refer to the PT/Dr, who will proceed with the treatment, design/prescribe further management and document accordingly. League performance will also be collated from FAM at the end of the season as this has previously been associated with injury rates in other team sports [43].

Assessment of injury behaviours, team medical practice, injury risk, nutritional data, and mental health assessment will be done at three time points: at the beginning before the trial begins, halfway through the trial, and at the end of the season. Football exposure and surveillance data will be collected and collated at the end of each training session and/or match until the end of the season.

*Measurement of potential confounders*. Despite all players playing in the same league and at the same level, primary confounders for injury risk include physical/ anthropometric characteristics; existing mental health or psychiatric conditions and home environment, which may influence the SMHAT- 1 values, for example. Secondary confounders include playing experience, playing position, and playing level as well as socio-economic status, which will affect nutrition, menstrual hygiene management and private management of injuries. Where possible, these will be considered in the analyses. Some of them will also be explored further in the qualitative interviews at closure of the protocol.

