In the event of a participant being flagged as being at risk of self-harm or harm to others in the mental health screening, the Football Nurses and their supervisors will be obliged to provide brief intervention within the scope of their practice, following which they will refer the participant for further management by the relevant healthcare providers. Should a medical condition be detected in the physical assessments, a similar approach will be taken in the management of the player.

*Data analysis*. Data will be analyzed using the IBM Statistical Package for Social Sciences (SPSS) version 21. The Shapiro-Wilk test for normality of the data will be conducted. Baseline comparability of participants for potential confounding factors such as age, length of football career, and baseline injury risk will be conducted using a chi-square test (for categorical variables) and either independent t-tests [normally distributed data] or Mann-Whitney U tests [non-normally distributed data] (for continuous variables).

Due to the relatively small number of clusters, data analyses will be based on summary level measures to account for the shortcomings of individual level regression methods. The primary variable of interest will be sports medicine practice. The mean (SD) sports medicine practice score will be calculated and presented by cluster and by arm. The mean of these mean scores and their associated 95% confidence intervals (CI) will then be presented for each arm. Linear regression of the mean sports medicine practice scores per cluster and per arm; two-way analysis of variance (ANOVA), will be used to explore the differences in sports medicine practice score and the 95% CI associated with the FIFA Football Nurse intervention by arm.

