For the testing data such as injury risk (FMS, musculoskeletal screening), nutritional data (24h recall), and mental health assessment (SMHART-1), a mixed between-within-subjects ANOVA will compare the two arms over the whole intervention, then a post hoc Bonferroni test will be used to determine whether there are significant changes in the various scores and at what time point during the intervention these occur. Should there be a significant change in test scores, a one-way ANOVA will be performed at the specific time point to determine which specific test is different between arms. Additionally, a mixed effects logistic regression model will be used to examine the effects of arm assignment (intervention vs control) and time for categorical outcomes (e.g., sports injury prevention behaviours). To assess adherence and feasibility, descriptive statistics will be used to determine which aspects of the FIFA Football Nurse programme are best or worst implemented. Sensitivity analyses include adjustment for baseline team sports medicine practice and other potential confounding factors (e.g., previous injury, age, football experience, BMI, socioeconomic status). We will also include tests for effect-modification by relevant factors.

Additionally, data from the semi-structured interviews will be transcribed verbatim and a thematic analysis will be conducted using Braun and Clarke’s 6 step model [44] to group common themes and describe the experiences of women’s football stakeholders, and the barriers and facilitators towards the football nurse task-sharing approach. Analysis will be approached inductively by tagging meaning units which will then listed as themes, compared, and clustered to form categories, then assigned as general dimensions. Inter-rater reliability checks will be conducted by a blinded researcher, who will code a subset of the manuscripts and determine congruence of resulting themes. If clustering effects are observed in the data, these will be accounted for using appropriate statistical methods such as multilevel or hierarchical models.

All statistical tests conducted in this trial will be two-sided and p-values of < 0.05 will be considered statistically significant.

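### The three-step ANOVA plan for the continuous testing scores names no baseline-adjusted arm contrast: its arm main effect would be diluted to two thirds, and its later-visit comparison is significance-gated

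*Protocol article*

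**What the plan says.** The protocol article, under Secondary outcome measures, fixes the schedule: "Assessment of injury behaviours, team medical practice, injury risk, nutritional data, and mental health assessment will be done at three time points", namely "at the beginning before the trial begins, halfway through the trial, and at the end of the season". The project time frame dates these visits June, October and December 2022.

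The Data analysis text then sets three steps for the injury-risk, nutrition and mental-health scores:

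1. "a mixed between-within-subjects ANOVA will compare the two arms over the whole intervention, then a post hoc Bonferroni test will be used".
2. "a post hoc Bonferroni test will be used to determine whether there are significant changes in the various scores and at what time point" these occur.
3. "Should there be a significant change in test scores, a one-way ANOVA will be performed at the specific time point", to find which test differs between arms.

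The text does not say whether step 1 means the arm main effect or the arm-by-time interaction. No step adjusts a score for its own baseline. The only baseline adjustment named is elsewhere and concerns a different variable: "Sensitivity analyses include adjustment for baseline team sports medicine practice and other potential confounding factors". Categorical outcomes, by contrast, are given a mixed effects logistic model. The software is "IBM Statistical Package for Social Sciences (SPSS) version 21".

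**The concern.** A randomised comparison of a continuous score measured once before and twice during follow-up should give one stated arm difference, at a stated time, that uses the baseline value to gain precision. The sequence here does not. Its first step can be read as an average over all three visits, one of which cannot carry an effect. Its last step, the only one that compares the arms at a given visit, is run only after an earlier result is significant. The trigger is a significant change in scores, which could be a seasonal change common to both arms.

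The method also affects who is analysed. Classical between-within ANOVA needs a complete set of visits for each player. Some loss is plausible: the injury-risk tests include planks to exhaustion and timed push-ups and squats, which an injured player may be unable to do. Data collection also runs through the nurse in intervention teams and through a designated team member in control teams.

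At stake are precision and clarity on these secondary outcomes, and possibly bias. The primary analysis is not affected.

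**Working it through.** **Plan's own figure.** There is none for these scores; the sample-size section covers the primary outcome only. From it I take 12 teams × 25 players = 300 per arm (600 in all), purely as an illustration.

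**1. Dilution of the arm main effect.** The main effect is the mean of the visit-specific arm differences, and the expected difference at baseline is 0.
- Constant effect: (0 + 1 + 1)/3 = 0.667, against a post-baseline mean of 1. Ratio 2/3.
- Linearly growing effect: (0 + 0.5 + 1)/3 = 0.5, against a post-baseline mean of 0.75. Ratio 2/3.

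The interaction and a later-visit comparison do not contain this averaging.

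**2. Power of each reading (illustration).** Assumptions: 300 per arm, complete data, no clustering, unit SD, equal within-player correlation ρ between visits, two-sided 5%, constant effect δ. δ is set so that a baseline-adjusted comparison of the mean of the two later visits has 90% power: δ = (1.960 + 1.282) × √(2v/300), with v = (1 + ρ)/2 − ρ². This gives δ = 0.198, 0.187 and 0.159 at ρ = 0.3, 0.5 and 0.7.

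Per-player variances are (1 + 2ρ)/3 for the main effect (whose effect is 2δ/3), 1 for the one-way ANOVA at the final visit, and 1 − ρ² for the baseline-adjusted final visit. For a single contrast, power = Φ(effect/√(2 × variance/300) − 1.96). The interaction is a 2-df noncentral chi-square test.

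| Analysis | ρ = 0.3 | ρ = 0.5 | ρ = 0.7 |
|---|---|---|---|
| Arm main effect, three visits | 0.600 | 0.465 | 0.305 |
| Arm-by-time interaction | 0.553 | 0.656 | 0.740 |
| One-way ANOVA, final visit, gate ignored | 0.679 | 0.630 | 0.494 |
| Baseline-adjusted, final visit | 0.720 | 0.754 | 0.777 |
| Baseline-adjusted, mean of later visits | 0.90 | 0.90 | 0.90 |

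With an effect that grows linearly, the corresponding values are 0.600, 0.465, 0.305 (main effect); 0.686, 0.787, 0.859 (interaction); 0.899, 0.863, 0.737 (one-way, final visit); and 0.924, 0.942, 0.953 (baseline-adjusted, final visit). The ranking of the baseline-adjusted final-visit contrast above the three planned readings is the same. Real power would be lower throughout once clustering is counted, so only the comparison between rows matters.

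**3. Players with complete visits.** The document gives no attendance figure, so these rates are assumptions, with independence between visits.

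| Attendance per visit | All three can be missed (p³) | Only the two later can be missed (p²) |
|---|---|---|
| 90% | 73% | 81% |
| 85% | 61% | 72% |
| 80% | 51% | 64% |

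**4. Does deleting incomplete players bias the result?** Simulation: 200,000 players per arm, ρ = 0.5, true effect 0.30 SD at both later visits, about 70% of players complete. Arm differences among completers at baseline, mid and end of season:
- missingness at random: 0.00, 0.30, 0.31;
- missingness related to score equally in both arms: −0.01, 0.28, 0.29;
- missingness related to score in one arm only: −0.17, 0.13, 0.19.

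In the last case the three-visit average is 0.05 in place of the expected 0.20, while change from baseline to final visit shows 0.36 in place of 0.30. The direction of any bias therefore depends on the contrast.

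**The case against.** The best defence is that the protocol never names the arm main effect. The Bonferroni step asks at which visit changes occur and the one-way ANOVA is visit-specific, so the authors may have had the interaction or a later visit in mind, and neither is diluted. That stands. A reader might infer that all these effects are diluted or biased toward zero; the text does not establish it. What remains is that each available reading has its own weakness, as the power table shows.

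A reader might also infer that the plan drops players and reports on selected completers. The document does not say so. It is silent on deletion, imputation and attrition, and missing-data rules may sit in an analysis plan not shown. Complete-case use follows from the named method, not from stated text. Nor can it be presumed that injury, and so absence, differs by arm: that would be a trial result. Dietary recall and mental-health screening are not physical tests, so injury need not prevent them.

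An unadjusted one-way comparison of randomised arms is not biased by lack of baseline adjustment; it loses precision. An omnibus test followed by post hoc tests is also conventional.

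Finally, the protocol prefers cluster summaries because teams are few, and a player-level mixed model must answer that. It can, with small-sample degrees of freedom. A baseline covariate would also exclude players without a baseline score unless that is handled. Both points are taken into the fix.

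**Conclusion.** The concern holds in conditional form. The stated sequence fixes no single baseline-adjusted arm contrast for the continuous scores. If the arm main effect is reported, it is exactly two thirds of the mean post-baseline effect, given no effect at baseline. The interaction avoids this but yields no single estimate. The later-visit one-way ANOVA avoids it but is significance-gated and less precise: in the constant-effect illustration, final-visit power is 0.679, 0.630 and 0.494 against 0.720, 0.754 and 0.777 with baseline adjustment, at within-player correlation 0.3, 0.5 and 0.7.

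The share of players with complete visits rests on assumed attendance. Material bias from losing the rest needs missingness that relates to score differently by arm, for which the document gives plausible routes but no evidence. The outcomes are secondary, so this should be changed but does not threaten the primary conclusion.

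**What to change.** For each continuous score, replace the three-step sequence with one linear mixed model of the mid- and end-season values:

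- fixed effects for arm, visit, arm-by-visit, baseline score and region (the draw is made by region);
- random intercepts for team and player;
- every available post-baseline value used;
- small-sample degrees of freedom, such as Kenward-Roger or Satterthwaite, for the 24 teams.

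Keep players with a missing baseline score by a simple rule fixed in advance, for example mean imputation or a constrained longitudinal model. Report the end-of-season arm difference with its 95% CI whether or not any other test is significant, and drop the gated one-way ANOVA.

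The model remains valid when missingness depends only on scores already observed; it does not cure loss that depends on unobserved values. The cost is revised analysis wording and slightly more modelling work. No new data are needed. Check beforehand that the chosen software version provides the degrees-of-freedom method named.

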#### Sample size

The study aims to evaluate the impact of the Football nurse intervention on team sports medicine practice. Hence, the study will recruit twelve (12) nurses, with one assigned to each intervention team, and six (6) physiotherapists and/or doctors to supervise the Football Nurses from two teams each.

To determine the appropriate sample size, the study used the cluster randomized formula as in previous studies [38]. This formula considers the intra-cluster correlation coefficient, number of participants, expected effect size, and power of the study. The formula is as follows:

$$C=1+{\left(Z_{\alpha /2}+Z_{\beta }\right)}^{2}\frac{\left[\sigma_{0}^{2}+\sigma_{1}^{2}\right]\times [1+(m-1)k]}{m{\left(\mu_{0}-\mu_{1}\right)}^{2}}$$

Where C is the number of clusters required per treatment arm, *Z*_*α*/2_ and *Z*_*β*_ are the critical values of the standard normal distribution for the desired confidence level and power, respectively, *m* is the number of individuals per cluster and *k* is the intracluster coefficient, *μ*_1_ and *μ*_0_ are the true means, and σ_1_ and σ_0_ are the standard deviations, of the outcome variable in the presence and absence of the intervention, respectively.

The design effect of a CRT is related to the intracluster correlation coefficient as follows:

DEFF=1+(m−1)k

Assuming a 95% confidence level (*Z*_*α*/2_ = 1.96), a power of 80% (*Z*_*β*_ = 0.84), an expected effect size of 0.19 (based on a 50% increase in team sports medicine practice), a standard deviation of 0.30, an intra-cluster correlation coefficient of *k* = 0.2, and 25 participants per cluster, the study estimates that it will need 12 clusters (teams) in both the control and intervention groups. Therefore, a total of 600 participants will be recruited, with 300 participants in each group. In summary, the study will recruit twelve (12) nurses and six (6) physiotherapists/doctors to supervise the intervention teams. The study will need 12 clusters (teams) in both the control and intervention groups, with a total of 600 participants (300 in each group) to detect a statistically significant change in team sports medicine practice at a 95% confidence level and 80% power, using the cluster randomized formula [38, 39].

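### Baseline team practice score is kept for sensitivity analyses only; adjusting for it in the primary model would gain precision if baseline and end-of-season scores correlate above about 0.2

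*Protocol article*

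**What the plan says.** The protocol article makes team sports medicine practice the primary outcome, evaluated at team level by questionnaire (Primary outcome measure). It is collected repeatedly: "Assessment of injury behaviours, team medical practice, injury risk, nutritional data, and mental health assessment will be done at three time points", namely before the trial, midway and at season end.

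For the primary comparison, the Data analysis section chooses summary measures per team because there are few clusters. Scores are averaged by team and then by arm: "The mean of these mean scores and their associated 95% confidence intervals (CI) will then be presented for each arm". The arms are then compared by linear regression of the team means and a two-way ANOVA. The second ANOVA factor is not named, and no baseline covariate is mentioned.

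Baseline practice enters later in the same section: "Sensitivity analyses include adjustment for baseline team sports medicine practice and other potential confounding factors".

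**The concern.** There are 12 teams per arm, so the arms can easily differ by chance in practice at the start of the season. The draw is made within region, which does not directly balance baseline practice. An unadjusted comparison of end-of-season scores carries whatever part of that chance difference persists, and this widens its confidence interval. Where a baseline measure of the same outcome predicts the final score, including it as a covariate removes part of that variation. The plan will hold this measure but keeps it out of the analysis that decides the result. What is at stake is the precision of the headline estimate.

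**Working it through.** **Inputs from the protocol (Sample size and Data analysis sections).**
- Difference: "an expected effect size of 0.19 (based on a 50% increase in team sports medicine practice".
- SD: "a standard deviation of 0.30", taken as equal in both arms.
- Clustering: "an intra-cluster correlation coefficient of *k* = 0.2, and 25 participants per cluster".
- 12 teams per arm; planned "at a 95% confidence level and 80% power"; two-sided 5% tests.

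**Input not in the protocol.** The correlation r between baseline and end-of-season team scores. It is assumed over 0 to 0.7.

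**Step 1: the plan's own figure.** The printed formula gives

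C = 1 + (1.96 + 0.84)² × (2 × 0.30²) × [1 + 24 × 0.2] / (25 × 0.19²) = 1 + 9.07 = 10.07,

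which rounds up to 11 teams per arm. The protocol states 12. The gap is one team per arm on the conservative side and does not affect this point.

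**Step 2: unadjusted comparison.** The SD of a team mean is 0.30 × √(5.8/25) = 0.1445. The standard error of the difference is 0.1445 × √(2/12) = 0.0590. A t-test on 24 team means has 22 df. Noncentrality is 0.19/0.0590 = 3.22, so power is 86.8%. The 95% CI half-width is 2.074 × 0.0590 = 0.122.

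**Step 3: adjusted for baseline.** The residual SD is 0.1445 × √(1 − r²), with 21 df. With this few teams the covariate will not be exactly balanced, which inflates the variance by about 1 + 1/20 = 1.05. So

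SE = 0.1445 × √(1 − r²) × √(2/12 × 1.05).

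At r=0.5 this is 0.0523, and the half-width is 2.080 × 0.0523 = 0.109. At r=0.7 the half-width is 0.090. The standard error falls by about 11% and 27% respectively, since 0.866 × 1.025 = 0.887 and 0.714 × 1.025 = 0.732.

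**Step 4: the other reading of the SD.** If 0.30 is the SD of one score per team, replace 0.1445 by 0.30 throughout.

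Power for a difference of 0.19:

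| Analysis | Team-mean SD 0.1445 | Team-score SD 0.30 |
|---|---|---|
| Unadjusted, 22 df | 86.8% | 31.7% |
| Baseline-adjusted, r=0 | 85.0% | 30.4% |
| r=0.2 | 86.4% | 31.4% |
| r=0.3 | 88.1% | 32.8% |
| r=0.5 | 93.3% | 38.5% |
| r=0.7 | 98.7% | 52.5% |

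Simulation at r = 0, 0.3, 0.5 and 0.7 agreed with these values to within about one percentage point. Setting (1 − r²) × 1.05 = 1 gives r = 0.22, so break-even is at about 0.2.

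**Step 5: adding region.** Eight teams per region, drawn alternately, gives four per arm in each region. Region then takes 2 further df, leaving 19. In the first column, power becomes 84.5% (r=0), 87.6% (0.3), 92.9% (0.5) and 98.6% (0.7) if region explains nothing. That is about half a point lower at most.

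**The case against.** The strongest reply is that this is a preference about efficiency. Under randomisation the unadjusted team-level comparison is valid. Chance imbalance does not bias it and is already reflected in its confidence interval. On the protocol's clustering assumptions it exceeds the planned 80% power, and the adjusted analysis is already announced. All of this stands. A reader might infer that the primary analysis is biased, or that omitting baseline leaves the trial underpowered, and the protocol supports neither. The 31.7% figure comes from reading 0.30 as the SD of a single team score, and adjustment would not restore 80% there at any r considered.

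A second reply is that r may be low. Clubs that already have medical personnel are excluded (Table 2), which may narrow the spread of baseline scores. This also stands, and it is why the range starts at zero, where adjustment loses power slightly.

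The third reply concerns timing. The Project time frame puts randomisation in May 2022 and baseline testing in June, the month the intervention starts. Under Standardisation of procedures, data come mainly through the nurse in intervention teams and through a designated team member in control teams. A baseline taken after allocation, and differently by arm, could bias an adjusted analysis. The Football nurse intervention section describes a survey before the nurses are trained, and the draw follows that training, but the text does not say that this survey is the baseline of the primary outcome. This objection stands as a condition on the fix.

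Finally, the unnamed second ANOVA factor could be region, so the comparison may not be unadjusted for region. If it is time, baseline scores would enter as a response, but covariate adjustment for baseline would still sit among the sensitivity analyses.

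**Conclusion.** The point holds as lost precision, not as an error. The protocol measures the primary outcome at baseline and explicitly assigns adjustment for it to sensitivity analyses. With a team-mean SD of 0.1445 and a difference of 0.19, moving it into the primary model changes power by about −2 points at r=0, +1 at r=0.3, +6.5 at r=0.5 and +12 at r=0.7. If 0.30 is the team-level SD, the changes are about −1, +1, +7 and +21 points. These figures rest on an assumed r, on the end-of-season score being the primary time point, on normal theory, and on a 22-df t-test as the reading of the planned comparison. Only the direction for r above about 0.2 is secure; the size of the gain is not known from the protocol.

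**What to change.** State in the Data analysis section that the primary model is a linear regression of the end-of-season team score on arm, baseline team score and region. Region belongs in the model because the draw is made within region. Keep the unadjusted comparison as the sensitivity analysis.

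The cost is 1 df for baseline and 2 df for region, with a loss of about 2 points of power if r is near 0. The analysis needs no data beyond the baseline questionnaire already planned, but the schedule has to support it. The questionnaire must be completed before the draw or, failing that, before any nurse contact and by the same procedure in both arms. The Project time frame should be amended to say so. If neither condition can be met, baseline adjustment should stay a sensitivity analysis.

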### Inclusion of nurses in task sharing in SEM

Perhaps, instead of having an SEM strategy that is heavily reliant on doctors and PTs as in HIC, we ought to adapt current global standards to fit the human resources profile of SSA and include the largest group of healthcare providers by numbers, nurses. In general medical practice, nurses currently conduct screening, diagnosis and management of medical conditions as well as referring to other healthcare workers as necessary and are an integral part of healthcare delivery in most LMICs [25, 30]. Similarly, they should be a key component to delivering health care services in football especially at grassroots levels and for underserved football players. Including nurses in the SEM practice agenda may help alleviate the shortage of pitch side medical care in women’s football teams. Additionally, as nurses are predominantly women [31], their inclusion into SEM practice will also help increase representation of African women SEM practitioners as they are still underrepresented in the profession [32].

Therefore, the aim of this project is to develop a task sharing approach (Football Nurse) to actively recruit and train nurses as pitch side responders in grassroots women’s football. Similar task sharing approaches have been used successfully in other sporting codes [33] and in LMICs to manage the diagnosis, treatment, and referral of other health conditions where there is a shortage of specialists [30]. The broad aim of this project is to explore the influence of trained nurses as pitch side responders in grassroots women’s football teams. Therefore, to minimise contamination, the unit of randomisation and analysis will be the football team.

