For the injury, illness, and medication use data, injury, illness, or medication use history will be recorded to determine the baseline injury, illness, or medication use risk. Injury, illness, and medication use rates and corresponding 95% CIs will be calculated for all players as the number of injuries/illnesses/medications reported per 1000 hours of football exposure (training and match). The severity of the injuries/illnesses, as scored by the number of days of missed training or matches, will also be calculated. Additional analysis will include, but not be limited to, the incidence and type of injury/illness/medication; chronic versus acute injuries/illnesses/medications; contact versus non-contact injuries and mechanism of injury (all per 1000 player hours). A Poisson regression will be used to compare differences in the injury, illness, or medication use rates between the control and intervention arms. To evaluate the impact of the FIFA Football nurse intervention on injury/illness/medication use outcomes, we will use logistic regression analysis to compare the proportion of players with injuries/illness/taking medications between the intervention and control arms, adjusting for potential confounding variables such as previous injury, age, playing experience, BMI, and playing conditions. We will also conduct subgroup analyses to determine whether the intervention has differential effects on different subgroups of players.

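### Secondary between-arm comparisons name models with no team term and adjust for clustering only if it is observed; in a trial that randomises teams the adjustment should be unconditional

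*Protocol article*

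**What the plan says.** The introduction of the protocol article (Inclusion of nurses in task sharing in SEM) states that "the unit of randomisation and analysis will be the football team". The Sample size section carries this through with a design effect and an ICC of 0.2. The Data analysis text (under Secondary outcome measures) then sets a general principle because clusters are few: "data analyses will be based on summary level measures to account for the shortcomings of individual level regression methods". It works that principle out for the primary practice score, which is averaged within each team before the arms are compared.

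For the secondary outcomes, the same text names these comparisons of arms:

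- Injury, illness and medication rates: "A Poisson regression will be used to compare differences in the injury, illness, or medication use rates between the control and intervention arms".
- Players affected: "we will use logistic regression analysis to compare the proportion of players with injuries/illness/taking medications between the intervention and control arms", with adjustment for player characteristics such as age, BMI and previous injury.
- Injury-risk tests, nutrition and mental health: "a mixed between-within-subjects ANOVA will compare the two arms over the whole intervention", followed by a one-way ANOVA at any time point that shows a change.
- Categorical outcomes such as prevention behaviours: a mixed effects logistic model, with the random effect not named.

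Team appears in none of the first three. The one sentence on clustering closes the paragraph on the interviews: "If clustering effects are observed in the data, these will be accounted for using appropriate statistical methods such as multilevel or hierarchical models". Significance is judged at a two-sided 5% level throughout: "All statistical tests conducted in this trial will be two-sided and p-values of < 0.05 will be considered statistically significant".

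**The concern.** Clustering in this trial comes from the design. Teams are allocated, so the variation between teams within an arm is the yardstick for any difference between arms, whether or not a look at the data reveals it. Here there are concrete reasons to expect it. Teammates share a home field. Surveillance is recorded by one nurse in each intervention team, or through one designated person in each control team, so differences between recorders become differences between teams.

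A rule that adjusts only when clustering is seen has two weaknesses. With 24 teams, a small ICC is often missed although it still inflates the error. And without a criterion, the analyst chooses the model after seeing the data. The rule also departs from the article's own statements on the unit of analysis and on summary measures.

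At stake is a chance difference between 12 and 12 teams being reported as an effect of the Football Nurse on injury, illness, injury risk, nutrition or mental health. These outcomes are secondary, but the abstract lists injury and illness incidence among the things the study will compare, and the article hopes the project will become a model for other countries.

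**Working it through.** **Inputs from the article.** 12 teams per arm; 25 participants per team for sizing (30 registered players per team elsewhere); ICC 0.2, SD 0.30 and effect 0.19, all given for the practice score; two-sided 5% level.

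**The article's own figure.** Its formula gives C = 1 + (1.96 + 0.84)² × (2 × 0.30²) × [1 + (25 − 1) × 0.2] / (25 × 0.19²) = 1 + 7.84 × 0.18 × 5.8 / 0.9025 = 10.07, so 11 teams per arm. The article states 12, one more per arm. That is on the safe side and does not matter here. What matters is that the sizing uses a design effect of 5.8, which the secondary models then leave out.

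**Assumptions.** No ICC is given for any secondary outcome, so 0.01 to 0.2 is an assumed range. The article does not define 'observed'; an F test between teams within arms at p<0.05 is assumed.

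**Formula with no adjustment.** DEFF = 1 + (m − 1)k, and true type I error = 2[1 − Φ(1.96/√DEFF)]. For m = 25 and k = 0.2: √5.8 = 2.41, 1.96/2.41 = 0.81, error 0.416. A nominal 95% interval then covers 58%, and 600 players carry the information of 600/5.8, or about 103.

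**Simulation.** 40,000 trials per ICC, continuous outcome, 12 against 12 teams of 25, no true effect. The conditional rule uses a team-level t test (22 df) when the F test is significant and the unadjusted test otherwise.

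| ICC | DEFF | No adjustment (formula) | Clustering detected | Conditional rule | Team-level t test |
|---|---|---|---|---|---|
| 0.01 | 1.24 | 0.078 | 20% | 0.066 | 0.050 |
| 0.02 | 1.48 | 0.107 | 42% | 0.072 | 0.050 |
| 0.05 | 2.20 | 0.186 | 87% | 0.060 | 0.051 |
| 0.10 | 3.40 | 0.288 | 99% | 0.051 | 0.050 |
| 0.20 | 5.80 | 0.416 | 100% | 0.050 | 0.050 |

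At ICC 0.03, clustering is detected in 62% of trials and the conditional rule gives 0.071. The simulated error with no adjustment agrees with the formula (0.418 at ICC 0.2). With 30 players per team the formula gives 0.084, 0.210 and 0.452 at ICC 0.01, 0.05 and 0.2. If the adjusted stage uses a normal instead of a t reference, the conditional rule gives 0.062 to 0.076 over the tabulated ICCs, and a team-level test with a normal reference gives about 0.063 even when adjustment is always made. This is why a small-sample reference is needed.

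**Scope of the figures.** They describe a cross-sectional comparison of arms on a continuous scale: directly the one-way ANOVA and the arm main effect, and only approximately the logistic and Poisson analyses. They do not describe the arm-by-time interaction, where team differences that stay constant over the season cancel.

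**The case against.** The best defence is that the article does commit to accounting for clustering that is seen. A reader might infer from the unadjusted models that the secondary results would carry a false-positive rate of 42 to 45% and are all invalid. The documents do not support that. Those figures need an ICC of 0.2, which is given only for the primary practice score, and they need adjustment never to be made. With a formal test, an ICC of 0.2 would be detected essentially always and the error would return to 5%. This part of the defence stands, and it sets the lower end of the size.

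Three further points also stand:

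- The level of the Poisson model is not stated, and for the surveillance data the article says "These data will be collected at a cluster level using injury, illness and football load forms as recommended in injury consensus statements", so it cannot be called a player-level model. The criticism survives in another form: a plain Poisson model ignores extra variation between teams whether it is fitted to players or to team counts.
- The mixed effects logistic model is not faulty. Its random effect is merely unnamed, a detail an article may leave to a fuller document.
- The placing of the clustering sentence after the interview text is editorial.

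One might add that a statistical analysis plan could settle all this. That does not answer the point. The article does not stay silent; it states a condition for adjustment, and the condition is wrong for a design that randomises teams.

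**Conclusion.** The rule is wrong as written, for the secondary outcomes only. A reader might infer that the trial's main conclusion is at risk; it is not on this ground, because the practice score is analysed on team means. The faulty comparisons are the Poisson regression, the logistic regression on players, the between-within ANOVA and the one-way ANOVAs.

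The size depends on how the undefined condition is applied. With a formal F test the excess over 5% is at most about 2 percentage points, largest near ICC 0.01 to 0.03, where clustering is often missed. If the models are run as named with no adjustment, the error rises from about 8% to a worst case of 42% over the assumed ICC range with 25 per team. The article commits to neither version, so the error rate of these tests is not controlled by the plan. The direction is certain for any positive ICC left unadjusted in a cross-sectional comparison of arms; the exact figure is not.

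**What to change.** Delete the condition and state that every between-arm comparison of a secondary outcome accounts for team, whatever the data show. Either of two routes suffices:

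1. **Team summaries.** Compute each team's rate per exposure hour, proportion affected or mean score. Compare the 24 values by arm with region in the model, since the draw is made within region, and use a t reference. An intercept, arm and two region terms leave 24 − 4 = 20 df. This follows the article's own preference for summary measures.
2. **A model with a team random effect** and a small-sample correction, where player covariates or repeated measurements are wanted. For the mixed effects logistic model, it is enough to say that the random effects include team.

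Data collection does not change. The cost is wider, correct confidence intervals and slightly more analysis work.
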